## Assignment of interventions: allocation

### Sequence generation {16a}

Following informed consent, participants will be randomized in a 1:1 allocation to a sequence of either immersion relaxation using VR or just taking a rest without immersion VR, based on a computer-generated random number that is concealed via a sealed envelope. One of the researchers will conduct this step. The allocation will not be disclosed to the other researchers who conduct the trial until the participants are enrolled and assigned. In addition, researchers who perform the statistical analyses will be blinded to the group allocation.

### Concealment mechanism {16b}

Once the consent form is received, a computer-generated random number from 1 to 140 will be assigned to that participant. Each number from 1 to 140 will be assigned a random group type: VR intervention or control. For the numbers randomly allotted for participants, the computer-generated random number assignment will be set such that it results in a 1:1 ratio, stratified by gender. The participant’s number will become the identifier for the participant’s collected data for data analysis. Once all participants have been enrolled and assigned, the list of which participants were distributed among the groups will be kept in an opaque, sealed envelope. Upon completion of consent, randomization, and baseline data collection, the participant will receive an opaque and sealed envelope associated with their randomized number. The researchers responsible for data collection and the analysis of outcomes will be blinded until after the completion of data analysis.

## Assignment of interventions: blinding

### Who will be blinded {17a}

The researchers responsible for data collection and the analysis of outcomes will be blinded until after the completion of data analysis because they will neither be involved in the assignment of subjects nor the implementation of the interventions.

### Procedure for unblinding if needed {17b}

Not applicable to the study; the design is open label with outcome assessors and data analysts being blinded so unblinding will not occur.

## Data collection and management

### Plans for assessment and collection of outcomes {18a}

Data will be collected from participants of two groups at three time points: baseline status (08:10 am, T1), before VR immersion (08:10, T2), and after VR immersion (08:40, T3) of the next day.

#### fNIRS

The fNIRS assessment will be employed to examine the cortical neural activity changes from the night shift and VR intervention. A multichannel near-infrared brain function imaging device (NirSmart, Danyang Huichuang Medical Equipment Co., Ltd., China) will be used to record changes of oxy-Hb and deoxy-Hb, and the emission light sources will be 730 nm and 850 nm, respectively. There are 23 emitters and 15 detectors to form 47 effective channels. The distance between channels is 3 cm, and the sampling rate of all channels is ≥11 Hz. The probe set will be placed on the scalp corresponding to the PFC, premotor and supplementary motor cortex, motor cortex, and sensory cortex, according to the international 10–20 system for electroencephalogram. The Cz and Fz positions from the 10–20 system are first identified. Detector D2 corresponds to the Fpz point. The midpoint of the connecting line between emitter S13 and emitter S14 corresponds to the Cz point (Fig. 3).

**Fig. 3 Fig3:**
[figure not shown]
Arrangement of the fNIRS probe array. The red and blue dots represent the sources and detectors, respectively. Green dots with digits represent the positions of the measurement channels.

All participants will be told to avoid medications that may affect brain activity for at least 24 h prior to the assessment. Prior to the assessment, the participants will be read instructions and perform a training module to ensure that they understand the study and know what to expect. During the fNIRS assessment, the participants will be seated, comfortably and relaxed, in front of a computer monitor in a warm, quiet, and slightly dark room. Participants will be guided to relax and to restrict their motions during the experimental paradigm.

#### VFT task

Studies have shown that fNIRS is sensitive enough to also detect small changes during VFT [17]. The VFT has been widely used to investigate impaired PFC activation or decreased cognitive performance [18, 19]. In this protocol, VFT will be employed to test cognitive functions while assessing PFC hemodynamics by fNIRS. Before the test, the test process will be explained to the subjects with a unified guide. The test will be performed in four stages, 160 s in total. The first stage is a prescanning period, 10 s in total. The subject focuses on the 10 cm×10 cm cross on the computer screen 70 cm in front and waits for the test to begin. The second stage is a repeat count period, lasting for 30 s. The participants stare at the 10 cm×10 cm cross on the computer screen and repeat counts from 1 to 5. The third stage is the listing word task period, lasting for 60 s, in which three simple Chinese characters (such as Da, Tian, and Bai) are prompted by machine voice, and the subjects list words that start with the character, each lasting for 20 s. Stage 4 is a repeat count period again, lasting for 60 s, and the subjects still repeat counts from 1 to 5. The behavioral performance will be assessed by the total number of correct words generated in the third stage. In this protocol, fNIRS assessments while executing the VFT task will be conducted at 3 time points (day duty, before intervention after the end of the night shift, and after intervention). To avoid the influence of memory on the results when performing the task repeatedly, the Chinese characters provided at the 3 time points will all be different.

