### Trial design {8}

The study is a parallel two-group randomized controlled trial comparing the mood, cognitive performance, and brain activation of medical staff who undergo and do not undergo VR immersion after a night shift. In addition, data collected from a day shift are assessed and serve as a normal baseline. A total of 140 volunteers (including physicians and nurses) will be randomized in a 1:1 allocation to the intervention group and the control group by the block randomization method. fNIRS and abbreviated POMS assessments will be used at three time points collected throughout the study to assess how night shift and VR restorative environment immersion affect frontal cortex activity and mood in physicians and nurses [15, 16]. The collection time points are as follows: the first is collected during the day shift which is at least 3 days after the last night shift, and the last two are collected in the morning after the night shift (at 8:00–9:00 am) before and after VR intervention/rest. The interval between day shift and night shift assessments is at least 14 days. The intervention group will undergo immersion relaxation by watching their favorite VR restorative environment video for 10 min at 8:30 am after the night shift, while the control group will rest quietly for 10 min awake. The timeline design of the study is presented in Fig. 1.

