## Interventions

### Explanation for the choice of comparators {6b}

To assess the damaging effects of the night shift, the brain activity, VFT performance, and mood state outcomes of the day shift will be compared with those after the night shift. To assess the beneficial effects of VR-based restorative environment intervention on mood, cognitive performance, and brain activity, those outcomes will be compared among pre- and post-VR intervention and simple relaxation.

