We acknowledge that there are some limitations in this study, because there may be an effect of proficiency on the results as each participant performed the VFT task a total of 3 times throughout the study protocol. Therefore, we developed different Chinese characters at each of the 3 assessment time points, and we expect this effect to be equal between the intervention and control groups, particularly as the researchers are blinded to participant allocation. In addition, the study is a single-center trial with a small sample size. Therefore, these preliminary results should be confirmed by conducting a lage- scale multicenter study.

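### As the article reads, each verbal fluency character set is tied to one time point, so the day-versus-night comparison mixes the night-shift effect with set difficulty and practice

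*Protocol article*

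**What the plan says.** Under VFT task, the protocol guards against memory effects by changing the prompts: "the Chinese characters provided at the 3 time points will all be different". The Discussion repeats this as "we developed different Chinese characters at each of the 3 assessment time points". Scoring is a word count: "The behavioral performance will be assessed by the total number of correct words generated in the third stage". That stage uses three prompt characters of 20 s each. Brain signals are recorded during the same task: "fNIRS assessments while executing the VFT task will be conducted at 3 time points".

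The order is fixed. Trial design {8} says of the assessments that "the first is collected during the day shift which is at least 3 days after the last night shift", and it places the other two on the morning after a night shift. The consent section {26a} puts baseline within a week of consent, and the concealment section {16b} puts it before the participant receives the envelope.

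The comparators section {6b} makes day versus night an aim for brain activity, VFT performance and mood: "mood state outcomes of the day shift will be compared with those after the night shift". Outcomes {12} lists fNIRS and VFT performance at the three time points as primary.

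The Discussion admits a possible proficiency effect and answers it in two ways: the prompts differ, and "we expect this effect to be equal between the intervention and control groups".

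**The concern.** How many words a person can list depends on the prompt characters as well as on the state of the person. If everyone meets one set on the day shift and another after the night shift, any difference in difficulty between the sets appears as a change between day and night. Practice from the first session changes at the same step.

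The Discussion's argument about equality between groups does not reach this comparison. Both arms work the night shift and both move from one set to the next together, so neither arm is a control for it.

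The error can go either way. A harder set after the night shift would be reported as impaired cognition; an easier set, or practice, could hide a real impairment. No analysis of the data can recover the split if set and time point coincide for every participant.

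**Working it through.** **The plan's own figure.** Sample size {14} uses d = 0.5, 80% power and two-sided 5%. By the normal formula, n per arm = 2(1.960 + 0.842)²/0.5² = 62.8, so 63. Allowing for 10% loss, 63/0.9 = 70 per arm, or 140 in total. The stated number reproduces. It concerns VR versus control, and the present point does not depend on it.

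**What the day-night difference estimates.** With T1 the day shift and T2 the morning after the night shift before the intervention:

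E(T2 − T1) = night-shift effect + (difficulty of set 2 − difficulty of set 1) + practice.

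With one set per time point and T1 always first, the three terms are aliased. For VR versus control, the set and practice terms are the same in both arms and cancel in expectation.

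**Size for VFT word count (illustration).** From the documents: 140 × 0.9 = 126 completers, two-sided 5%. Assumed, because the documents give no value: a paired test, within-person correlation r of 0.5 to 0.7, no true night-shift effect, no practice effect, and a set gap b in SD units.

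SE of the mean difference = √(2(1 − r)/126).
- r = 0.5: √(1.0/126) = 0.089 SD
- r = 0.7: √(0.6/126) = 0.069 SD

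The chance of a significant result (noncentral t, noncentrality b/SE) is:

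| Set gap b | b/SE, r = 0.5 | Rate | b/SE, r = 0.7 | Rate |
|---|---|---|---|---|
| 0 | 0 | 5% | 0 | 5% |
| 0.1 SD | 1.12 | 20% | 1.45 | 30% |
| 0.2 SD | 2.24 | 61% | 2.90 | 82% |
| 0.3 SD | 3.37 | 92% | 4.35 | 99% |

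**Simulation of the remedy.** With r = 0.6, 126 participants, 4,000 runs per gap, one set harder than the other two, and plain t tests throughout:

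| Gap | Day-night, fixed sets | Day-night, rotated sets | Between-arm change, fixed sets |
|---|---|---|---|
| 0.2 SD | 71% | 4.4% | 4.8% |
| 0.3 SD | 96% | 4.2% | 4.5% |
| 0.5 SD | 100% | 3.3% | 4.2% |

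Rotation removes the set bias, and the randomized contrast was sound already. The rotated rate falls below 5% because set variation enters the error term when the analysis has no term for set.

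**Why rotation needs a set term.** If one set is harder by b, rotation adds variance 2b²/3 to the change from T2 to T3 (the post-intervention assessment). At r = 0.6 the variance of that change is 2(1 − 0.6) = 0.8. For b = 0.2 the addition is 2(0.04)/3 = 0.027, about 3%. For b = 0.5 it is 2(0.25)/3 = 0.167, about 21%. Without a set term, this noise would fall on the VR-versus-control comparison.

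**The case against.** **The fixed link is the natural reading but is not stated outright.** Neither section says that every participant gets the same set at the same time point, and an article may leave stimulus lists and difficulty matching to the full protocol. This stands as a limit, so the point is conditional on that reading. It is still more than a missing detail: the article states the choice and defends it, and the defence fails for one of its own aims.

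**There are partial safeguards.** The prompts are described as simple, the score sums over three characters, and a training module precedes assessment. These may shrink a gap or a practice effect; none shows that the sets are equally hard.

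**The inputs to the illustration are assumed.** That is true of the gap and the correlation, hence the range. The pairing is assumed too, since the statistical section names only t tests. An unpaired test would need a difference of 1.96 × √(2/126) = 0.247 SD. With r = 0.5, a 0.2 SD gap would then be called significant in about 30% of trials, because (0.247 − 0.2)/0.089 = 0.53. The rates change with the test; the bias in the estimate does not.

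**Stronger readings that the documents do not support.** A reader might infer that the VR result is compromised; it is not, because both arms meet the same sets at the same times. A reader might infer that the sets are known to differ in difficulty; nothing says so. A reader might carry the rates over to fNIRS; no passage links prompt difficulty to the hemoglobin contrast or gives its size.

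**Conclusion.** The point holds for the within-person day-versus-night comparison of VFT word count, on the reading that one set is attached to each time point. Under the stated assumptions, a difficulty gap too small to notice (0.1 SD) raises the false-positive rate from 5% to about 20-30%, and 0.2 SD raises it to about 61-82%. The direction and size of any real gap are unknown. For the task-evoked fNIRS signal the same confounding is possible but cannot be quantified from the documents. A pre-to-post change read within one arm has the same weakness; the between-arm contrast does not. POMS does not use the characters and is unaffected. It would go too far to say that the design can tell nothing about the night shift: the contrast can be reported, but a difference, or its absence, cannot be attributed to the night shift alone. The change should be made, since it is cheap and protects a stated aim, but the randomized comparison does not depend on it.

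**What to change.** Keep the three character sets and rotate them across T1, T2 and T3, using the six possible orders balanced within each arm. Seventy per arm is not a multiple of six, so balance is to within one: four orders with 12 participants and two with 11 (4 × 12 + 2 × 11 = 70).

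Analyse both the time-point and the between-arm comparisons of VFT and fNIRS with a model that includes set, such as a mixed model or ANCOVA, in place of the plain t tests. Rotation then does not add set variance to the VR-versus-control contrast.

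Rotation does not remove practice. State in the protocol and the report that day versus night remains confounded with practice because T1 is always first, and interpret that contrast cautiously. If the sets are in fact already rotated or matched for difficulty, say so. If neither is the case and the sets cannot be changed, present the day-versus-night VFT and fNIRS results as descriptive.

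The cost is a rotation table for the task, 2 degrees of freedom for set, and a modest change to the stated t-test analysis. No additional participants or visits are needed.

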#### Abbreviated POMS

The abbreviated POMS includes seven mood state subscales: tension, anger, fatigue, depression, vigor, confusion, and esteem-related affect. It is a 40-item self-report measure that evaluates the current emotional mood state of participants. Participants will be asked to rate how they are currently feeling in response to each of the 40 adjectives on a 5-point Likert scale ranging from ‘Not at All’ to ‘Extremely’. The total mood distance (TMD) is calculated by [tension + depression + anger + fatigue + confusion] − [vigor + esteem-related affect], and finally adding a constant of 100. Overall, higher scores for TMD and negative mood states indicate higher negative mood. The abbreviated POMS has been revised in Chinese with reliability coefficients for the subscales ranging from 0.62 to 0.82, with a mean of 0.71 [16].

### Plans to promote participant retention and complete follow-up {18b}

Participants will be given a reminder (via e-mail and phone call) a week before to schedule the follow-up.

### Data management {19}

All participant data will be identified using the assigned trial identification number. Each trial identification number will have its own designated folders. Data collected from fNIRS and VFT tasks are conducted on a single laptop and will be automatically uploaded to their respective designated cloud storage databases immediately after each individual measurement. Abbreviated POMS assessments will be recorded digitally using a digital copy of the assessments and saved into their respective participant folders. All data collected throughout the study will be stored for at least 5 years. A master data sheet that collects all digital data and is organized by participant number and time point will be preprogrammed to conduct range checks for all data values collected.

### Confidentiality {27}

Data will be stored on the cloud server provided by the hospital which is already secured to ensure strict access. Only primary researchers who enroll participants or collect and analyze data and other principal members of the research team have access to the cloud database. Before the data are uploaded to the cloud, they will be organized based on trial identification numbers instead of group and individual names. Access to the database may be granted upon reasonable request from other researchers, study entities, or miscellaneous government-associated groups who wish to conduct prospective meta-analyses.

### Plans for collection, laboratory evaluation, and storage of biological specimens for genetic or molecular analysis in this trial/future use {33}

Not applicable to the study; no biological specimens will be collected.

## Statistical methods

### Statistical methods for primary and secondary outcomes {20a}

Data analysis will start after all recruited participants have completed their assessments. To avoid bias, the data analyst will be blinded to the data. Participants who successfully complete the study according to the intervention plan will be included in the analysis. Missing data or any data collected that does not adhere to the protocol will be eliminated from data analysis.

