### Additional consent provisions for collection and use of participant data and biological specimens {26b}

On the consent form, participants are asked if their data can be used even if they choose to withdraw from the trial. Participants are also asked for permission of the research team to share relevant data with personnel from regulatory authorities, where relevant. The trial does not involve the collection of biological specimens.

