### Intervention description {11a}

The intervention time point is approximately 8:30 am after the night shift. All participants will complete the fNIRS and abbreviated POMS first, which takes approximately 20 min. Participants in the intervention group will recline comfortably on a sofa, wearing a VR glass loaded with an intelligent VR psychosomatic interactive training system (Ruixin, Ruihai Yinuo Intelligent Technology Co., Ltd., China) and watch 360° panoramic videos of the immersive VR natural restorative environment selected according to their preferences to relax themselves in the resting room. The intervention time will be 10 min. After the intervention, all participants will complete the fNIRS and abbreviated POMS again. Participants in the control group also recline comfortably on a sofa but only rest for 10 min without VR immersion. After relaxation, all participants will complete the fNIRS and abbreviated POMS again.

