### Criteria for discontinuing or modifying allocated interventions {11b}

Participants may quit at any time due to various reasons including failure to meet inclusion criteria or inability to continue VR intervention.

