### Methods in analysis to handle protocol nonadherence and any statistical methods to handle missing data {20c}

Missing data and any data collected that does not adhere to the protocols will be removed from data analysis.

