### Adverse event reporting and harms {22}

It has been reported that a few people may experience physical discomfort, such as dizziness, when wearing VR glasses. Therefore, the trial can be stopped at any time if participants feel discomfort during the VR immersion, and the participants will be treated accordingly. The fNIRS system poses very little risk. Should an unforeseen serious adverse event occur, a case report will be written, and the trial manager will be notified within 24 h. All these events will be recorded and shared with the steering committee, ethics committee, and trial participants within the next 48 h. Participants will have the right to quit at any time for any reason during the trial.

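### The only analysis set is completers who followed the intervention plan, which leaves the randomised comparison open to bias because exclusion for VR intolerance can occur in one arm only

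*Protocol article*

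**What the plan says.** The protocol article settles the analysis set in its section on statistical methods for primary and secondary outcomes {20a}: "Participants who successfully complete the study according to the intervention plan will be included in the analysis". The next sentence adds: "Missing data or any data collected that does not adhere to the protocol will be eliminated from data analysis". The section on nonadherence and missing data {20c} gives the same answer: "Missing data and any data collected that does not adhere to the protocols will be removed from data analysis". No as-randomised set, imputation or sensitivity analysis is named anywhere in the article.

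Three other sections bear on who would be removed.
- Criteria for discontinuing {11b} gives as reasons for quitting "failure to meet inclusion criteria or inability to continue VR intervention".
- Adverse event reporting {22} notes that "a few people may experience physical discomfort, such as dizziness, when wearing VR glasses", and continues that "the trial can be stopped at any time if participants feel discomfort during the VR immersion".
- Intervention description {11a} says that controls "only rest for 10 min without VR immersion". Trial design {8} requires that rest to be quiet and awake.

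Randomisation follows consent and comes before the intervention (sequence generation {16a} and concealment mechanism {16b}).

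**The concern.** Randomisation makes the two arms comparable as assigned. A rule that keeps only those who completed the assigned procedure selects participants after randomisation, partly on a consequence of the treatment. A participant who takes the headset off because of dizziness leaves the VR mean. A control with the same susceptibility is never tested in that way and stays in the control mean.

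If those who stop would have had worse mood or fewer correct words afterwards, their removal flatters VR. The objectives {7} say that a positive result could encourage hospitals to adopt VR for staff in every department. That decision depends on the effect in everyone assigned to VR, including those who cannot finish it. Because the rule covers every outcome and no second analysis is planned, nothing in the reported results would show whether the exclusions mattered.

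**Working it through.** **1. The plan's own sample size.** Inputs from Sample size {14}: d = 0.5, two-sided 5%, 80% power, 10% loss, 140 in total. By the normal approximation, n per arm = 2 × ((1.960 + 0.842)/0.5)² = 62.8, so 63. Allowing for loss, 63/0.9 = 70 per arm, or 140. The stated figure reproduces. The 10% allowance protects precision. It does not correct selective exclusion.

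**2. Size of the bias.** The documents give no intolerance rate and no link between intolerance and outcome, so both are assumptions here:
- there is no true VR effect;
- a share p of the VR arm, the least tolerant, is excluded, and no controls are;
- intolerance has correlation r with a poorer outcome.

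Bias in SD units = r × φ(z)/(1 − p), where z is the (1 − p) quantile of the standard normal and φ its density. Type I error comes from the noncentral t with 70(1 − p) against 70 participants and noncentrality bias/√(1/(70(1 − p)) + 1/70).

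For p = 10%: z = 1.282, φ(z) = 0.1755, and 0.1755/0.9 = 0.195. With r = 0.5 the bias is 0.0975 SD. The standard error is √(1/63 + 1/70) = 0.174, so the noncentrality is 0.56 and the type I error 8.6%.

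| Excluded from VR arm | r | Bias (SD) | Share of d = 0.5 | Type I error |
|---|---|---|---|---|
| 3% (about 2 people) | 0.3 | 0.021 | 4% | 5.2% |
| 3% | 0.5 | 0.035 | 7% | 5.5% |
| 10% (7 people) | 0.3 | 0.058 | 12% | 6.3% |
| 10% | 0.5 | 0.098 | 20% | 8.6% |

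**3. Cross-check by a second route.** If a share q is removed whose mean would have been g SD worse than that of those kept, the bias is q × g. With q = 10% and g = 1 this is 0.10 SD, with type I error 8.9% by the normal approximation. With q = 3% and g = 0.5 it is 0.015 SD and 5.1%. The two routes agree in scale.

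**4. Power if everyone randomised is analysed.** If a share q of the VR arm gains nothing but is measured, the effect becomes 0.5 × (1 − q). Power of the t test at 70 v 70 is 83.6% for q = 0, 79.7% for q = 5% (d = 0.475) and 75.3% for q = 10% (d = 0.45).

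**The case against.** The strongest reply is that the filter applies to both arms. Controls must rest awake, reclining on a sofa, after a shift that ran from 17:00 to 8:00. Some may fall asleep and be removed as non-adherent. If these are the most fatigued controls, their removal flatters the control mean and works against VR. This stands. A reader might infer that the trial would compare those who tolerate VR with all controls, but the rule does not say that. Only removal for VR intolerance is confined to one arm. The calculation above, which excludes no controls, leaves out any such offset.

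Second, the article speaks only of a few people with discomfort, and the exposure is a single 10-minute session. At 3% excluded the inflation is negligible. This also stands, and it is why the range has to start there.

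Third, a reader might infer that every outcome is tilted towards VR. The documents do not support that. Nothing in them says which way headset dizziness moves oxy-Hb or deoxy-Hb, the outcomes named in the sample size section. Mood is a secondary outcome.

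Fourth, the Discussion puts understanding of neural mechanism above promotion of the technology, and a completer comparison has some relevance to mechanism. That justifies keeping it as a secondary view. It does not restore the comparability that randomisation gave.

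Two defences do not hold. The rule is stated twice, so it is not a detail left to an analysis plan. Blinding of the analyst does not help when the exclusion is itself a result of the treatment.

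The consent form question, in which "participants are asked if their data can be used even if they choose to withdraw from the trial", is only weak support for the concern, because it does not say which data or which analysis.

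**Conclusion.** The concern holds as a fault in a stated rule. A completer, adherent-only set is the sole analysis of a randomised superiority comparison, and one foreseen exit occurs after randomisation and in the VR arm only. The accurate wording is that the comparison is open to bias. A reader might go further and conclude that the result is biased, but without an intolerance rate or a known link to outcome the documents cannot show that.

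The likely direction is towards VR for mood and verbal fluency, and unknown for oxy-Hb and deoxy-Hb. Under the stated assumptions the size runs from negligible at 3% excluded to as much as a fifth of the planned effect at 10%. Exclusions among controls could reduce it. The rule still needs changing before analysis, because the plan holds no other analysis that would reveal the problem, and T3 data never collected from those who stop cannot be recovered.

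**What to change.** Reword {20a} and {20c} along these lines:
- The primary analysis includes all randomised participants in the arm assigned, whether or not the 10 minutes of VR or rest were completed as planned.
- Participants who stop VR and are willing are asked for the T3 assessment already scheduled at 08:40.
- A missing T3 is handled by a stated method that uses T1 and T2, such as a mixed model or multiple imputation.
- fNIRS recordings are excluded only on signal quality, judged blind to arm.
- The completer analysis is kept as a sensitivity analysis.
- Exclusions and their reasons are tabulated by arm.

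The cost is revised wording and a little more analysis work, with no added visits. There may also be some loss of power. If those who stop gain nothing, power at 70 v 70 and d = 0.5 falls from 83.6% to 79.7% when they make up 5% of the VR arm, and to 75.3% at 10%. These figures assume that T3 is obtained from everyone.
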